### Trial visits

The trial includes a total of nine study visits during the operation and the postoperative period. The inclusion and exclusion criteria will be evaluated during the screening visit (the day before the operation). After the patient has given his or her informed consent, the demographic and baseline data, medical history, current medication, comorbidities, American Society of Anaesthesiologists (ASA) classification, and ECOG status will be evaluated and documented. Randomization will be performed intraoperatively by authorized study personnel, and intraoperative parameters will be collected.

Patients are followed up until discharge. Study visits will be scheduled on postoperative days 1 to 7 and on the day of discharge from the hospital. There will also be a daily visit by the pain service until the epidural catheter is removed. Primary and secondary endpoints and (serious) adverse events (SAEs and AEs) will be evaluated and documented during each visit and documented on the case report form (CRF). All planned study visits are summarized in Table 2. Data from patients without RAMIE (conversion, inoperability) will be documented until the time of the operation (visit 1). Routine blood tests (including haemoglobin concentration, leucocyte count, and serum C-reactive protein) will be performed during the postoperative visits on PODs 2, 4, and 6. In addition, postoperative chest X-rays are performed routinely on postoperative days 1, 3, and 6 independent of the study intervention or additionally according to the clinical course. According to the protocol, a CT scan of the thorax or abdomen or diagnostic endoscopy will not be routinely performed during the study period. These diagnostic examinations are only indicated based on a medical rationale (e.g. control scan of pneumothorax before or after chest drain removal, suspected fluid collection or abscess, elevated C-reactive protein or leucocyte count, suspicion of anastomotic leakage).

**Table 2 Tab2:** Study visits

Documentation	Screening day of admission	Day of operation	PODs 1–7 or until epidural catheter is removed	Day of discharge
Inclusion criteria	X			
Exclusion criteria	X	X		
Patient characteristics	X			
Randomization		X		
Surgical technique		X		
NRS pain scale			X	
Morbidity			X	X

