## Methods

### Aim of the study

This study aims to evaluate two different chest drain management strategies in patients undergoing RAMIE for oesophageal cancer with regard to perioperative complications until discharge. The study’s primary objective is to investigate whether the intensity of postoperative pain can be significantly reduced by avoiding chest and abdominal drains within 3 h after RAMIE, resulting in a drainless postoperative course. We assume that this will influence secondary endpoints such as early recovery and length of hospital stay.

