#### Secondary endpoints

The secondary endpoints reflect important treatment outcomes and thus enable a comprehensive evaluation of the surgical therapy and the postoperative course of treatment.

Perioperative complications associated with oesophagectomy are defined and recorded according to the Oesophagectomy Complications Consensus Group (ECCG) definition [20]. The secondary endpoints are pain according to NRS in the period from POD 1 to 7 (daily, Table 1), mean postoperative pain (NRS) on POD 2–4, additional (> standard) analgesic drug use during POD 2–4, drain secretion volumes, operating time, blood loss, conversion rate, number of postoperative chest X-ray and computed tomography (CT) scans, interventions including chest CT drain or chest tube replacement, postoperative mobilization (steps per day as measured with an activity tracker), and time to functional recovery. Time to functional recovery will be defined as the postoperative time point at which the following criteria are fulfilled: absence of all wound/chest drains and no requirements of intravenous analgesics and tolerance of oral intake and ability to mobilize independently.

**Table 1 Tab1:** Determination of postoperative pain during study visits

Abdominal pain?	NRS 0-10
Chest pain?	NRS 0-10
Others?	NRS 0-10
Pain on exertion?	NRS 0-10
Maximum pain since surgery?	NRS 0-10
Minimal pain since surgery?	NRS 0-10
Is your mobility or movement impaired by the pain?	Yes/no
Is the pain affecting your ability to cough or breathe deeply	Yes/no
Did the pain wake you up during the night	Yes/no
Is your mood affected by the pain?	Yes/no
Have you felt very tired since the operation?	Yes/no
Have you suffered from nausea since the operation?	Yes/no
Have you vomited since the operation?	Yes/no
Would you have liked to have more painkillers received?	Yes/no
How satisfied are you with the pain treatment you have received since the operation?	0–10°

0 = very dissatisfied; 10 = very satisfied

Furthermore, oesophagectomy-associated postoperative morbidity (pneumothorax, pleural effusion, chylothorax, pneumonia, anastomotic leakage, surgical site infection), in-hospital mortality, length of intensive care unit (ICU) stay, and hospital stay will be analysed. Postoperative morbidity from index surgery to discharge will be assessed using the comprehensive complication index based on the Clavien‒Dindo classification.

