### Assessment of safety

Adverse (AEs) and serious adverse events (SAEs) will be recorded during this trial.

An SAE is defined as any life-threatening adverse event, which requires or prolongs hospital stay, results in persistent or significant disability or incapacity, or results in death. Events occurring in the period from randomization to discharge must be documented and reported to the coordinating investigator within 5 days after they become apparent. All SAEs must be documented on a “serious adverse event form”.

The form contains the following information: name of the attending physician, detailed description of the SAE, consequence for the trial, and dated signature of the attending physician.

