### Data collection

After the patient gave his or her informed consent, the demographic and basic data (sex, age, weight, height, medical history, current medication, comorbidities, ASA classification, ECOG status), and primary tumour characteristics (UICC classification, date of diagnosis, location, previous treatments including chemotherapy, target therapy, radiotherapy, and surgery) are evaluated and documented by the investigator. Intraoperative parameters such as length of operating time, blood loss, blood transfusion requirement, and conversion to open surgery are recorded.

During each study visit and on the day of discharge, primary and secondary endpoints and SAEs are evaluated and documented according to the eCRF. During the postoperative visits, routine blood tests (including haemoglobin concentration, leucocyte count, and serum C-reactive protein) will be performed. Furthermore, data that will be collected within these study visits include at least the following: postoperative assessment, ICU length of stay, grading of complications according to Clavien‒Dindo Classification, morbidity and mortality within the hospital stay, length of hospital stay, drain secretion volumes, postoperative examinations (e.g. chest X-rays, CT scans), and physical activity of the patient. The physical activity of the patients is collected using a CE-certified fitness tracker device, which measures the number of steps, distance, and activity minutes during the hospital stay. The transmission of these data works automatically via synchronization with a tablet or is carried out by the investigators before discharge.

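### Complications, deaths, re-interventions and SAEs are counted only until discharge, although the trial expects the intervention to bring discharge forward

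*Protocol article*

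**What the plan says.** Under Trial visits the article states "Patients are followed up until discharge", and the schedule has no contact after that: "Study visits will be scheduled on postoperative days 1 to 7 and on the day of discharge from the hospital".

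The individual outcomes follow the same limit:
- **Morbidity** (Secondary endpoints): "Postoperative morbidity from index surgery to discharge will be assessed using the comprehensive complication index".
- **Mortality** (Secondary endpoints): "in-hospital mortality, length of intensive care unit (ICU) stay, and hospital stay will be analysed". Data collection repeats the limit: "morbidity and mortality within the hospital stay, length of hospital stay, drain secretion volumes".
- **SAEs** (Assessment of safety): "Events occurring in the period from randomization to discharge must be documented and reported".
- **Re-interventions** (Secondary endpoints): "interventions including chest CT drain or chest tube replacement". No separate window is given, so they end with follow-up.

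The treatment is also expected to affect the date of discharge. The Background hypothesises that avoiding chest drains shortens hospital stay, the Discussion repeats this, and Aim of the study adds: "We assume that this will influence secondary endpoints such as early recovery and length of hospital stay". Length of stay is itself a secondary endpoint. The Blinding section says that participants, surgeons and outcome assessors cannot be blinded.

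**The concern.** A between-arm comparison of event counts needs both arms to be observed over the same period. Here the period ends at an event that the trial expects the treatment to bring forward. If intervention patients go home earlier, they have fewer days in which a complication can be counted, so the arms can differ in counted morbidity with no difference in true risk. The discharge decision is also taken in the knowledge of allocation.

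Separately, a readmission, a pleural re-intervention or a death after discharge is recorded in neither arm, whatever the length of stay.

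This bears on what the trial can conclude. Aim of the study and the Discussion frame the comparison in terms of perioperative complications, and the Abstract promises evidence on the feasibility of the drainless course. Pain on POD 2 cannot supply that evidence; the morbidity and safety outcomes have to. A later analysis plan cannot repair the gap, because the missing events would never have been collected.

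**Working it through.** **1. The plan's own figure, and whether it is touched.** Inputs from Statistical considerations and sample size calculation: NRS 5 versus 4 on POD 2, SD 1.4, two-sided 5%, power 80%, dropout 10%. The exact two-sample t-test calculation gives 31.76, so 32 per group (power 80.3%). 32/0.9 = 35.6, so 36 per group and 72 in total. The stated figure is reproduced. The primary endpoint is at a fixed day, so neither it nor the 72 depends on the follow-up window.

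**2. What is seen in both arms in any case.** Trial visits schedules visits on POD 1 to 7 and chest X-rays on POD 1, 3 and 6 regardless of arm. Events in roughly the first week are therefore largely captured. The exposed events are those between the earlier and later discharge dates, and those after discharge.

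**3. Illustration of size.** The article gives no length of stay and no complication rate, so all of the following are assumptions:
- the true 30-day risk R is the same in both arms;
- time to event is exponential with scale m, truncated at 30 days;
- discharge falls on a fixed day in each arm, unrelated to the patient's health.

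The share of 30-day events that occur by day x is

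F(x) = (1 − exp(−x/m)) / (1 − exp(−30/m)).

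The counted risk is R·F(discharge day). R and the denominator cancel, so the ratio of intervention to control is

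(1 − exp(−x_int/m)) / (1 − exp(−x_con/m)).

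m is not the mean event time once the distribution is truncated. The true mean is m − 30·exp(−30/m)/(1 − exp(−30/m)): 5.8, 8.4 and 10.3 days for m = 6, 10 and 15.

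| Discharge day, intervention vs control | m = 6 | m = 10 | m = 15 |
|---|---|---|---|
| equal | 1.00 | 1.00 | 1.00 |
| 9 vs 10 | 0.777/0.811 = 0.96 | 0.593/0.632 = 0.94 | 0.451/0.487 = 0.93 |
| 10 vs 12 | 0.811/0.865 = 0.94 | 0.632/0.699 = 0.90 | 0.487/0.551 = 0.88 |
| 8 vs 12 | 0.736/0.865 = 0.85 | 0.551/0.699 = 0.79 | 0.413/0.551 = 0.75 |

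In absolute terms, for an assumed R = 40% and m = 10, day 8 versus 12 gives F(8) = 0.551/0.950 = 0.580 and F(12) = 0.699/0.950 = 0.735. Counted risk is then 23.2% versus 29.4%, with no true difference. Over a common 30-day window F(30) = 1 in both arms, and the ratio is 1.00.

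**The case against.** **The window is declared and used consistently.** The stated aim itself limits complications to the hospital stay. A reader might infer that the protocol contradicts itself; it does not. This is a choice of secondary endpoint that could be improved, and that part of the objection stands.

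**The size is conjectural.** This also stands. The gap in discharge days drives the result, and the documents give none. A one-day gap does little, and a four-day gap has no support in the text. Discharge is also not independent of health: complications prolong stay, and unwell patients are normally kept in, so risk after discharge is probably lower than the illustration assumes.

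**Early harm is captured.** Fixed visits and X-rays in both arms cover the first week, including the period after early drain removal. A reader might infer that the harms specific to early removal appear mainly after discharge; nothing in the article supports that.

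**Drain-free time.** A reader might also argue that the arms are unequally observed because drains leave at 3 h in one arm and, by the standard algorithm, not before POD 6 for the second drain in the other. That difference is the treatment contrast itself. Strategies are compared from randomization or surgery, and a fixed window would not equalise drain-free days.

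**Small numbers.** With 36 per arm one might warn against reading non-significance as safety. The article makes no such claim, and the matter is separate from the window.

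**Kaplan-Meier.** The method is listed for secondary endpoints as appropriate. It does not cure the problem: censoring at discharge is related to the patient's condition, and post-discharge events remain unobserved.

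None of this removes the central point. Under the trial's own hypothesis the end of observation depends on treatment, and the article provides no contact after discharge.

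**Conclusion.** The concern holds for the secondary morbidity and safety comparisons only. If the intervention shortens stay, as hypothesised, counted risk is biased in its favour under the assumptions above: ratios of about 0.93-0.96 (day 9 vs 10), 0.88-0.94 (day 10 vs 12) and 0.75-0.85 (day 8 vs 12), for m = 6 to 15 days. With equal stay in both arms this bias is nil on average, though late events are still missed. These figures are illustrations, not estimates for this trial.

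The documents do not support reading this as a flaw in the primary analysis or as proof that the morbidity results will be materially distorted. It is an inexpensive improvement that should be made, because uncollected events cannot be reliably recovered at the analysis stage.

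**What to change.** Assess the CCI, mortality, readmission, pleural re-intervention and SAEs over one fixed window from surgery for every patient, for example 30 days, whatever the date of discharge. Obtain the data by one telephone call or records check. Make this window the main between-arm morbidity and safety comparison, and keep the in-hospital counts as descriptive. Amend Secondary endpoints, Trial visits, Assessment of safety and Data collection to agree.

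Cost: a formal amendment with ethics review and a registry update (both required under Trial design, study registration, and ethics), possibly a change to consent wording to cover post-discharge contact or records, and one contact or records check for each of 72 patients. No treatment rule, procedure, sample size or primary analysis changes.

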### Assessment of safety

Adverse (AEs) and serious adverse events (SAEs) will be recorded during this trial.

An SAE is defined as any life-threatening adverse event, which requires or prolongs hospital stay, results in persistent or significant disability or incapacity, or results in death. Events occurring in the period from randomization to discharge must be documented and reported to the coordinating investigator within 5 days after they become apparent. All SAEs must be documented on a “serious adverse event form”.

The form contains the following information: name of the attending physician, detailed description of the SAE, consequence for the trial, and dated signature of the attending physician.

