#### Data Monitoring Board (DMB)

In case of any irregularities, for example, concerning the prevalence or type of adverse events or serious adverse events reported to the principal investigator, the members of the independent DMB will be informed without any delay. The independent DMB will receive regular reports about major complications after 20 and 40 patients have been randomized. The results of the risk and safety analysis will be reported to the principal investigator, including recommendations concerning the continuation or termination of the trial.

Monitoring will be conducted according to approved standard operating procedures, which include personal site visits with verification of source data. Clinical monitoring in the RESPECT study will be performed according to the International Conference of Harmonization (ICH) Good Clinical Practice (GCP) guidelines by the Study Center of the Department of Visceral, Thoracic, and Vascular Surgery of the University Hospital and Medical Faculty Carl Gustav Carus, Dresden. The monitoring procedures are predefined in a study-specific monitoring manual and adapted to the study-specific risks for the patients. Regular on-site monitoring visits are planned at all sites depending on the recruitment rate and quality of the data (approximately one visit per site and year). The investigator must allow the monitor to look at all essential documents and must always provide support to the monitor. Study progress, recruitment, and data capture will also be reviewed at the leading centre by the principal investigator and study coordinators.

The role of the Steering Committee is to provide overall oversight of the trial and ensure that it is conducted according to the rigorous standards as outlined in the Guidelines for Good Clinical Practice.

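### As worded, the SAE definition makes threat to life a precondition, so events that only prolong stay or only disable fall outside SAE classification and the SAE form

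*Protocol article*

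**What the plan says.** The rule is in the Protocol article, Assessment of safety. The section opens by saying that "Adverse (AEs) and serious adverse events (SAEs) will be recorded during this trial". It then defines seriousness: "An SAE is defined as any life-threatening adverse event, which requires or prolongs hospital stay, results in persistent or significant disability", with incapacity and death completing the list. Two duties follow. One is a time limit: "Events occurring in the period from randomization to discharge must be documented and reported to the coordinating investigator within 5 days" of becoming apparent. The other is a form: "All SAEs must be documented on a “serious adverse event form". The section lists what the form contains (the physician, a description of the event, its consequence for the trial, a signature) and mentions no list of seriousness criteria on it.

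Three other sections bear on the same events:

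- **Secondary endpoints** includes "oesophagectomy-associated postoperative morbidity (pneumothorax, pleural effusion, chylothorax, pneumonia, anastomotic leakage, surgical site infection") and "interventions including chest CT drain or chest tube replacement", together with length of stay and a comprehensive complication index up to discharge.
- **Trial visits** has both AEs and SAEs evaluated and documented at each visit.
- **Data Monitoring Board (DMB)** has an ad hoc trigger, "In case of any irregularities, for example, concerning the prevalence or type of adverse events or serious adverse events reported to the principal investigator", and scheduled reports on major complications after 20 and 40 randomized patients.

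No section sets out the seriousness criteria as separate alternatives.

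**The concern.** The definition decides which events go on the SAE form, so it is an operative rule and not background text. Its grammar makes threat to life the entry condition. Prolonged stay, disability and death then describe or qualify an event that is already life-threatening; they are not independent routes to seriousness.

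That matters in a trial whose stated aim is to compare drain strategies with regard to perioperative complications. A pneumothorax, an effusion or a replaced chest tube can lengthen a stay without threatening life, and the literal sentence leaves out exactly that kind of event. Two centres take part at the start and others may join. If one applies the sentence as written and another reads it as a list, the same event is serious at one site and not at the other.

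**Working it through.** The plan gives no figure on this point, so the check is textual.

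**Step 1. What the sentence requires.** Three readings are possible.

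- Reading A: the relative clause restricts. The event must be life-threatening and must also meet one of the listed outcomes.
- Reading B: because of the comma, the clause only describes. The event must be life-threatening; the rest is commentary.
- Reading C: the items are meant as alternatives. Any one of them is enough.

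| Adverse event | A | B | C |
|---|---|---|---|
| Prolongs stay, not life-threatening | not SAE | not SAE | SAE |
| Disables, not life-threatening | not SAE | not SAE | SAE |
| Life-threatening, none of the listed outcomes | not SAE | SAE | SAE |
| Life-threatening and prolongs stay | SAE | SAE | SAE |

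The first two rows do not depend on how the comma is taken. Under either grammatical reading, an event that only prolongs stay or only disables is not an SAE. Only reading C includes it, and the sentence does not say C.

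**Step 2. What follows for such an event.** Compare the provisions one by one, for a pneumothorax that needs a new chest tube and lengthens the stay without threat to life.

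| Provision | Depends on the SAE definition? | Literal reading |
|---|---|---|
| SAE classification | yes | lost |
| SAE form | yes | lost |
| Report within 5 days | unclear | kept if the sentence covers all events, lost if it means SAEs only |
| AE record (Assessment of safety; Trial visits) | no | kept |
| Secondary endpoints, complication index | no | kept |
| DMB ad hoc trigger | no, it names AEs as well | kept |
| DMB reports after 20 and 40 patients | no, it names major complications | kept |

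The 5-day row is open because the sentence speaks of events in general but stands between the SAE definition and the SAE form rule.

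**Step 3. Is there a number?** The documents report no rate of drain-related events after RAMIE. The nearest figure, in the Discussion, is 2.8% recurrent effusion after video-assisted thoracic surgery with a 500 ml threshold, which is a different operation and setting. Applied to the 36 intervention patients it gives 0.028 × 36 = 1.0. A purely assumed rate of 10% to 20% gives 0.10 × 36 = 3.6 to 0.20 × 36 = 7.2. So the range runs from about 1 to about 7 patients, depending entirely on the assumption. The finding does not rest on it.

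**The case against.** The best reply is that this is a drafting slip. The items look like the usual seriousness criteria, and if threat to life were really required, naming prolonged stay and disability would add little. Trained staff may well read them as alternatives. That is probably what was intended, and it makes the correction uncontroversial. It does not make the written rule right, because sites are asked to apply the sentence and nothing else in the article corrects it.

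The second reply is that the events are caught elsewhere. This largely stands, as Step 2 shows. Two limits remain. Trial visits includes AEs at each visit, but Data collection names only endpoints and SAEs for the eCRF, so the AE route is not stated consistently. And the scheduled DMB reports come at two fixed points in recruitment, so they do not replace a prompt individual report.

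The third reply concerns comparability. The SAE count is not a listed endpoint, and randomization is stratified by site, so a site that applies one reading consistently applies it to both arms. That also stands: different readings between sites blur pooled totals but need not bias the comparison. Classification that differs by arm is conceivable, since data collectors and assessors know the allocation, but nothing in the article shows that it will occur.

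**Conclusion.** The point holds in a limited form. The SAE sentence is conjunctive as written. It takes events that only prolong stay or only disable out of SAE classification and off the SAE form, and it invites sites to classify the same event differently. Whether the 5-day report is lost as well depends on what the reporting sentence covers. The primary endpoint, the sample size and the efficacy analysis are not touched.

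A reader might infer three stronger things, and the documents support none of them:

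- **That prolonged stay is the main expected harm of early drain removal.** The article never says so. It hypothesises a shorter stay, and mentions drain reinsertion only as a historical concern and recurrent effusion only from lung surgery.
- **That some number of SAEs, such as 4 to 7, would go unreported.** That figure needs an assumed rate of 10% to 20%, and such events would still be recorded as AEs and as endpoints. They would lack the SAE label and form.
- **That the DMB would be blind to them.** Its ad hoc trigger names AEs alongside SAEs, and its scheduled reports are not tied to the SAE definition.

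The conclusion assumes that sites work from the wording shown. The full protocol and the SAE form are not at hand and may word the criteria differently.

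**What to change.** Keep the four existing criteria but set them out as alternatives. An SAE is any adverse event that:

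- (a) is life-threatening, OR
- (b) requires or prolongs hospital stay, OR
- (c) results in persistent or significant disability or incapacity, OR
- (d) results in death.

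Check that the SAE form uses the same four criteria, and align it if it does not. In the same edit it would help to say whether the 5-day limit applies to all adverse events or to SAEs only.

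The cost is one sentence and a few more SAE forms. Under the article's own rule for modifications, the change goes through a formal amendment with ethics review and notice to the centres. No treatment, visit or analysis changes.
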